### 8.5 Analysis Plan of Reported AEs/SAEs

The study lead will conduct real time analysis of the data including rates and confidence intervals using the ODK system. (See **Section 8.9**) Adverse events will be coded per the WHO Adverse Reaction Terminology (WHO-ART) and Medical Dictionary for Regulatory Activities (MedDRA). They also be defined according to level of severity (mild, moderate, severe) as defined in Section 8.4. The study will create an independent Data Safety Monitoring Board (DSMB) composed of members of the FMOH as well as national and international medical experts. (See **Appendix 12: Charter of Data and Safety Monitoring Board**) As a safety measure, the study lead will convene an immediate teleconference with the medical doctor participating in the study and the DSMB given the following criteria:

- IF the rate of adverse events ranked as mild/moderate by participants differs significantly in the trial group as compared to the control group during the first two “Follow-up Days” (**Day 2, Day 4**) as well during subsequent review of the data at **Day 15**, and at the conclusion of the study on **Day 31** (to determine if the remainder of the worda can safely be treated via triple drug therapy).
- IF an SAE occurs, the study lead and the medical doctor will conduct an immediate analysis and convene a call with the DSMB members. The DSMB members will advise the medical doctor in making an initial decision about attribution and whether a formal DSMB meeting is required. (Note: Given that a “severe” adverse event includes inability to complete daily activities, it will be classified as a possible SAE for the purposes of this study.)
- At conclusion of the study on Day 31 (to determine if the remainder of the worda can safely be treated via triple drug therapy).

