The causal relationship of serious adverse events observed with the triple therapy will be assessed as: *Unrelated, Unlikely, Likely*. The study will utilize information collected by the clinical nurses using the “Conduct an AE Investigation” steps detailed in the Serious Adverse Event Handbook. It is important to note that the study will not follow-up “minor” or “moderate” adverse events up with the full investigative checklist prescribed by the handbook but will reserve this for “severe” adverse events and SAEs. The PI, supervisors, and independent monitors will meet to review these determinations. If the supervisory group questions the results of the clinical nurses’s investigations, it will perform its own investigation of the report as an addendum to the original report. Incidences will be analysed based on preferred terms and body system levels. “Severe” adverse events and SAEs occurring during exposures will be analysed based on 3 levels of selection per pre-existence and causality:

- Treatment emergent signs and symptoms (TESS), i.e., all AE during exposure to treatment or that were not pre-existing
- TESS without causality ‘unlikely’
- TESS with causality ‘likely’

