**4. Causality assessment criteria:**

4.1. **Is the serious effect related to the therapy?** 1. Not related 2. Probably 3. Unlikely

4.1.1. **What is your Arguments for decision.....**

4.1.2. Remarks/Observations regarding this serious adverse effect case management.....

.....

**NOTE: Serious adverse effects will be treated and observed for 24 hours (maximum) by the physicians on the field. If there is no improvement, the subject will be transferred to the most appropriate health care facility**

Thank you for your collaboration

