### ***Terms of Reference (ToR)***

1. The DSMB for the Co-administration trials are charged with the safety and well-being of the study participants. They also serve as advisors on maintaining data quality and unanticipated study events.
2. The study will generate real time analysis of the data collected and reports including rates and confidence intervals (See **Section 8.9**). As a safety measure, the study leaders will convene an immediate teleconference with the DSMB given the following criteria:
  - IF the rate of adverse events ranked as mild/moderate by participants differs significantly in the trial group as compared to the control group during the first two “Follow-up Days” (**Day 2, Day 4**) as well during subsequent review of the data at **Day 15**, and at the conclusion of the study on **Day 31** (to determine if the remainder of the woreda can safely be treated via triple drug therapy).
  - IF an SAE occurs all related data will be provided to the DSMB members who will make an initial decision about attribution and whether a formal DSMB meeting is required. (Note: Given that a “severe” adverse event includes inability to complete daily activities, it will be classified as a possible SAE for the purposes of this study.)
  - At conclusion of the study on **Day 31** (to determine if the remainder of the woreda can safely be treated via triple drug therapy).
3. If the DSMB concludes that there is evidence that warrants stopping the trial or a change in the procedures of the clinical trial, the Board will be responsible for drafting a report of their recommendations to the Principal Investigators and to the IRB of the LSHTM and AHRI. If there is no concern, the Board will also issue a report stating they have no concerns.
4. The DSMB shall meet by phone at Day 31 regardless of the occurrence of AEs and SAEs for the purposes of reviewing the accumulated data, the quality of the information collected the safety of the trial procedures and the efficacy of the treatment arms. The committee shall issue a summary report, which will be forwarded to the Co-administration study PIs, the Federal Ministry of Health of Ethiopia, and the LSHTM and AHRI IRB.

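### Section 8.5 and the DSMB charter name different deciders for initial SAE attribution and for calling a formal DSMB meeting, and the causality rating behind two analysis tiers is not pinned down

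*Protocol*

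**What the plan says.** Section 8.5 describes what happens after an SAE: "the study lead and the medical doctor will conduct an immediate analysis and convene a call with the DSMB members". It continues: "The DSMB members will advise the medical doctor in making an initial decision about attribution and whether a formal DSMB meeting is required". A severe adverse event follows the same path, because "it will be classified as a possible SAE for the purposes of this study".

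The DSMB charter covers the same step in item 2 of its Terms of Reference. There the related data go to the "DSMB members who will make an initial decision about attribution and whether a formal DSMB meeting is required".

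Later in section 8.5, causality is rated for SAEs seen with the triple therapy as *Unrelated*, *Unlikely* or *Likely*, using information that the clinical nurses collect. Then: "The PI, supervisors, and independent monitors will meet to review these determinations". If that group questions the nurses' result, "it will perform its own investigation of the report as an addendum to the original report". Severe events and SAEs are then analysed in three tiers: all treatment-emergent events, those not rated *unlikely*, and those rated *likely*.

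The SAE recording form (Appendix 5, item 4.1) asks "Is the serious effect related to the therapy" and offers *Not related*, *Probably* and *Unlikely*.

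**The concern.** Section 8.5 and the charter use almost the same sentence with a different person in charge. In one, the trial's doctor decides and the board advises. In the other, the board decides. Whether a formal meeting is needed is a question of oversight, and section 8.5 gives it to a member of the team being overseen.

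The second issue is the rating itself. Two of the three tiers consist of whatever events carry a given causality label. Three features make that label uncertain:

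- It is described for one arm only, although the tiers are useful only as a comparison of arms.
- An event can carry the nurses' investigation and a later one from the supervisory group, with nothing to say which one enters the table.
- The form on which causality is recorded has no *Likely* box.

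The arm is visible by design: one group takes three drugs together, the other has two rounds two weeks apart, and teams and monitors are assigned by arm. Where a rating can be revised by people who know the arm, the rule for which version counts should be fixed in advance.

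**Working it through.** No stated figure is in dispute, so the check is a comparison of texts.

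**Step 1. Who decides.**

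| Decision | Section 8.5 | Charter, Terms of Reference item 2 |
|---|---|---|
| Initial attribution | Medical doctor, advised by the DSMB | DSMB members |
| Whether a formal DSMB meeting is needed | Medical doctor, advised by the DSMB | DSMB members |

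The event, the two decisions and the stage (initial) are the same. If doctor and board disagree, each text gives a different outcome. The charter's section on meetings, which lets the Chair schedule further teleconferences, sits more easily with the charter rule than with section 8.5.

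**Step 2. Which rating feeds the tiers.**

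| Source | Who | Scale | Scope |
|---|---|---|---|
| 8.5, SAE bullet | Doctor, advised by DSMB | none given | any SAE, with severe events classed as possible SAEs |
| Charter, item 2 | DSMB | none given | the same |
| 8.5, causality paragraph | Nurses' investigation, then PI, supervisors and independent monitors | *Unrelated, Unlikely, Likely* | rating stated for SAEs under triple therapy; tiers cover severe events and SAEs |
| Appendix 5, item 4.1 | The investigator completing the form | *Not related, Probably, Unlikely* | SAE form |

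Tier 1 needs no rating. Tier 2 depends on who is rated *unlikely*, and tier 3 on who is rated *likely*. Tier 3 cannot be filled directly from the form, because *Probably* first has to be mapped to *Likely*. No passage assigns a final attribution.

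**Step 3. What is not touched.** The primary outcome (section 10) is the incidence of AEs/SAEs over one month and states no causality filter. The 1.5% margin and the sample size therefore do not depend on this rating.

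**Step 4. How many people pass through the step.** Inputs from sections 6 and 8.1: an adverse event rate of 7%, and 13,680 to 16,000 participants.

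- 0.07 × 13,680 = 958 people with an adverse event
- 0.07 × 16,000 = 1,120 people with an adverse event

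The protocol gives no severe share. Assuming 1% to 5%:

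- low end: 0.01 × 958 ≈ 10
- high end: 0.05 × 1,120 = 56

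So roughly 10 to 56 people would need attribution. This shows how often the step is used, not how many ratings would differ between the two rules.

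**The case against.** The strongest reply is that the board is well protected whichever sentence is followed. Section 8.5 requires a call with the DSMB for every SAE. The charter lets a member request full-committee review of an event that the member considers a serious issue, lets the Chair call further teleconferences, and fixes a Day 31 meeting regardless of events. All of this stands. A reader might infer that the doctor could keep the board from meeting; the documents do not support that.

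A reader might also infer that only events the supervisory group questions are reviewed, and only by trial staff. Neither is right. The group reviews the determinations in general; only its own re-investigation is conditional. It includes independent monitors, whom section 8.6.3 draws from academic institutions in Ethiopia and abroad.

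The steps in section 8.5 can be read as a sequence: initial decision, nurse investigation, group review. That is fair, and it means the group review need not be a rival rule. It does not settle the doctor-or-board conflict, since both sentences concern the same initial decision.

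Finally, which of two ratings enters a table could be left to a statistical analysis plan. That is reasonable, and silence on it alone would not be a finding. The points that stand are things the protocol itself states: two deciders for one decision, a causality rating described for one arm, and two scales that do not match.

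**Conclusion.** The contradiction between section 8.5 and the charter is certain from the wording and should be reconciled. The causality paragraph also needs tightening, because tiers 2 and 3 of the severe AE/SAE analysis rest on a rating that is described only for the triple-therapy arm, may exist in two versions, and is collected on a different scale.

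The size is moderate. The problem touches secondary safety tables and the formal route to a DSMB meeting. It does not alter the primary comparison, the margin or the sample size. About 10 to 56 people would pass through attribution, on the assumed severe share of 1–5%.

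It is tempting to express the stakes as the shift in an upper confidence bound when one related SAE is added or removed. That would show what one event does to any small count, not what the wording conflict does, and the protocol plans no such bound. Nor do the documents support making the DSMB the sole final adjudicator from narratives with the arm removed. The charter gives it an initial decision with all related data, and drug and timing information bears on attribution.

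**What to change.** 1. In section 8.5, replace the clause in which the board advises the doctor with the charter wording, so that the DSMB makes the initial attribution and decides whether it formally meets.
2. In the causality paragraph of section 8.5, apply the same assessment to every severe adverse event and SAE in both arms.
3. Name one rating as the one used in tiers 2 and 3. The DSMB's attribution is one option, with the nurse, doctor and supervisory-group ratings kept as recorded opinions. If the analysis plan already names it, a cross-reference is enough.
4. Give item 4.1 of the SAE form the same categories as section 8.5.

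The cost is a few sentences, one form item and slightly more correspondence with the DSMB. Little new work arises, because section 8.5 already calls the board for each SAE and both texts class severe events as possible SAEs. Arm-stripped narratives are not required.

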## 10 Timetable for Study Completion

[figure not shown]

The Primary outcome is

- The safety as can be measured by incidence of AEs/SAEs over one month following the co-administered MDA in comparison to a control group receiving the standard MDA regimen.

Secondary Outcomes are:

- Understanding the perceptions of the beneficiaries receiving the co-administration of azithromycin, ivermectin, and albendazole especially surrounding pill burden and the change in MDA distribution schedule.
- Understanding the perceptions of the co-administration strategy by the local health workforce as a means of PC-NTD drug delivery.
- A cost analysis comparing existing MDA unit costs from woredas within the region already on a standard MDA schedule with that of the co-administered woredas.

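### Section 8.5 states its causality grading for serious events under triple therapy only, yet two of its three TESS tiers select severe and serious events by that grade with no arm limit

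*Protocol*

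**What the plan says.** Protocol Section 8.5 introduces the causality scale with these words: "The causal relationship of serious adverse events observed with the triple therapy will be assessed as" Unrelated, Unlikely or Likely. No sentence there extends the scale to the control arm.

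The same section then sets out how severe adverse events and "SAEs occurring during exposures will be analysed based on 3 levels of selection per pre-existence and causality". The three tiers are all treatment-emergent signs and symptoms, those left after removing events graded *unlikely*, and those graded *likely*. No arm is named. The full investigation that supplies the evidence is also not tied to an arm: the study "will reserve this for “severe” adverse events and SAEs".

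Other places speak of attribution in arm-neutral terms. Earlier in Section 8.5, any SAE triggers a call, and "The DSMB members will advise the medical doctor in making an initial decision about attribution". The DSMB charter says: "IF an SAE occurs all related data will be provided to the DSMB members who will make an initial decision about attribution". The SAE form (Appendix 5) asks whether the event is related to the therapy, but offers Not related, Probably and Unlikely. Its lead-in question asks about events after the three drugs were taken.

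The primary outcome, given under Section 10, is "incidence of AEs/SAEs over one month following the co-administered MDA in comparison to a control group receiving the standard MDA regimen". It carries no causality condition.

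**The concern.** The trial exists to compare the safety of two ways of giving the same drugs. A causality grade helps that comparison only if it is assigned in both arms by the same rule. Here the grade is stated for one arm and for serious events, but it is used to select both severe and serious events wherever they occur.

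If field staff follow the sentence as written, a control-arm SAE has no value on the scale. It cannot enter the *likely* tier, and the protocol does not say how an ungraded event is treated in the middle tier. A severe but non-serious event has the same problem in either arm. A table of related events by arm would then partly reflect who was graded rather than what happened. Serious events will probably be few, so a handful of missing grades could change how such a table reads.

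**Working it through.** The plan gives no figure on this point to reproduce. The check is to set the texts side by side and follow the literal rule through the three tiers.

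**Step 1. Scope of each text**

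| Place in the protocol | Arm | Events | Grades |
|---|---|---|---|
| 8.5, causality sentence | triple therapy | serious | Unrelated, Unlikely, Likely |
| 8.5, TESS tiers | no limit | severe and serious | uses Unlikely and Likely |
| 8.5, full investigation | no limit | severe and serious | none named |
| 8.5, DSMB call | no limit | any SAE (severe AEs count as possible SAEs) | none named |
| DSMB charter, Terms of Reference | no limit | any SAE (same note on severe AEs) | none named |
| Appendix 5, lead-in question | worded for the three drugs | serious or severe | none |
| Appendix 5, causality item | no limit (the therapy) | serious | Not related, Probably, Unlikely |

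The first two rows differ in both arm and event type, and the second depends on the first.

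**Step 2. Do the other rows supply the missing grade?** The DSMB call and the charter produce an initial attribution decision, but they name no scale and no link to the tiers. The form does not offer *Likely*, so the third tier cannot be filled from it without a mapping that the protocol does not give. Section 8.8 says the control arm goes through its process twice, but that refers to the distribution and surveillance schedule, not to causality grading.

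**Step 3. Consequence of the literal rule.** Suppose each arm truly has S serious and V severe non-serious treatment-emergent events. In the trial arm, a share a of the serious events is graded *Likely* and a share b *Unlikely*. Only the trial arm's S events are graded.

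- Tier 1 (all TESS): S + V against S + V. No distortion.
- Tier 2, if ungraded events are kept: (1 − b)S + V in the trial arm against S + V in control. Control looks worse.
- Tier 2, if ungraded events are dropped: (1 − b)S against 0. The trial arm looks worse.
- Tier 3 (*likely*): aS against 0. The trial arm looks worse.

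The direction is therefore clear for tier 3. For tier 2 it depends on a rule for ungraded events that the protocol does not state. If S = 0, tier 3 is empty in both arms whatever the severe events were, because V is never graded.

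**Step 4. Size.** The documents give none of S, V, a or b. The earlier studies summarised in Section 4 report no serious events, so S could be close to zero, and no rate of severe events is given. No numerical distortion can be derived.

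**The case against.** The strongest reply is that the triple-therapy wording is shorthand. The protocol often describes the trial arm and then carries the process to control: Section 8.7 and the last house-to-house visit in Section 8.8 also mention only people given the triple treatment, yet the title of Table 3 covers both arms. Attribution on the DSMB call, in the charter and on the form is not limited to an arm. Investigation of severe events and SAEs has no arm limit, and each arm has an independent monitor (Sections 8.6 and 8.6.3). Severe events are classed as possible SAEs, which might bring them under the grading sentence.

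Much of this stands as evidence of intent. It does not complete the rule: none of these places assigns Unrelated, Unlikely or Likely to a control-arm event. Section 8.5 also lists severe events and SAEs as separate groups, so a possible SAE is not plainly a serious event for grading. How the tiers are tabulated could be left to a statistical analysis plan, but that plan cannot recover grades that were never assigned.

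A reader might infer more: that control-arm events receive no attribution at all, that the between-arm comparison is wrong by construction, or that the DSMB's comparison is spoiled. The documents do not support these readings. Arm-neutral attribution exists for any SAE. No formal between-arm test of related events is specified. The between-arm trigger for the DSMB concerns mild and moderate event rates, which do not use the tiers.

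**Conclusion.** The gap is real and limited. As written, the formal scale covers serious events under triple therapy, while tiers 2 and 3 apply it to severe and serious events without an arm limit. Read literally, those two tiers are not comparable between arms. Grading in both arms was probably intended, but the text does not say so, and the passages that point that way carry either no scale or different grades.

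Tier 1, the proportion with an AE in each arm (Section 8.9) and the primary AE/SAE incidence comparison do not use causality and are unaffected. The conclusion rests on literal application of the causality sentence. No magnitude is claimed, because the documents give neither the number of such events nor the share in each grade. The point should be corrected before grading starts, since the fault is in a comparative safety display and is cheap to remove.

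**What to change.** Replace the causality sentence in Section 8.5 with: *The causal relationship of all severe AEs and SAEs in both arms (after each of the two control-arm rounds) will be assessed by the same group with the same scale and procedure.* State that all three TESS tiers apply to both arms.

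In Appendix 5, reword the lead-in question so that it fits a control participant who has received only one of the two rounds, and give the causality item the same grades as Section 8.5.

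The cost is one sentence in the protocol, two edits to a form, and review by the existing supervisory group of a small number of additional control-arm events. No extra staff are needed, because investigation and review already carry no arm limit.

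### Section 8.5 ties the causality grade to serious events under triple therapy but builds causality tiers with no arm limit; the same grading should be stated for both arms

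*Protocol*

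**What the plan says.** Section 8.5 of the protocol contains both the grading rule and the analysis that uses it.

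- Grading: "The causal relationship of serious adverse events observed with the triple therapy will be assessed as" Unrelated, Unlikely or Likely. This is the only place where the protocol sets that scale.
- Analysis: severe "adverse events and SAEs occurring during exposures will be analysed based on 3 levels of selection per pre-existence and causality". The first tier is all treatment-emergent events. The second is "TESS without causality ‘unlikely" and the third is "TESS with causality ‘likely". No arm is named.
- Attribution when an SAE occurs, also in 8.5: "The DSMB members will advise the medical doctor in making an initial decision about attribution and whether a formal DSMB meeting is required". No arm is named.
- The DSMB charter (Appendix 10, Terms of Reference, item 2) has the same trigger but a different decider: "IF an SAE occurs all related data will be provided to the DSMB members who will make an initial decision about attribution".
- Later review in 8.5: "The PI, supervisors, and independent monitors will meet to review these determinations".

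The SAE form (Appendix 5, item 4.1) asks whether the serious effect is related to the therapy, without naming an arm. Its lead-in question (item 3.5) is worded for someone who has taken all three drugs. Section 8.8 says the control arm goes through the same surveillance process twice, first for ivermectin and albendazole and then for azithromycin.

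**The concern.** The trial compares two arms, and the severe and serious events are the part of the safety profile that a programme deciding on adoption will read most closely. A causality filter is informative in such a comparison only if it is applied in the same way to both arms. Section 8.5 words the grade for one arm and then uses it to select events with no arm limit. If the field team takes the grading sentence at its word, the second and third tiers have no valid control counterpart, and they err in opposite directions for reasons unrelated to the drugs. The question is whether the protocol really sets a one-arm rule, and how far the damage would reach.

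**Working it through.** The plan gives no figure to reproduce. The check compares the passages and then works through what the tiers do to ungraded events.

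**1. Which events get the grade?**

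| Place | Events covered | Arm |
|---|---|---|
| 8.5, grading sentence | serious events | triple therapy named |
| 8.5, three tiers | severe AEs and SAEs | none named |
| 8.5, trigger when an SAE occurs | any SAE | none named |
| Appendix 10, item 2 | any SAE | none named |
| Appendix 5, item 4.1 | serious effect | none named |
| Appendix 5, item 3.5 | serious or severe event | worded for all three drugs taken |

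The grading sentence is the narrow one. The other attribution passages are wider, but they do not set the Unrelated/Unlikely/Likely code that feeds the tiers. The two DSMB passages describe an initial decision, made alongside whether to convene a formal meeting.

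**2. Does the form fit the control arm?** Control participants take ivermectin and albendazole first and azithromycin two weeks later. In the first control round nobody has taken three drugs, so item 3.5 does not fit as worded. After the second round it does.

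**3. What do the tiers do if control events stay ungraded?** Assume E severe or serious treatment-emergent events in each arm (identical arms), every triple-arm event graded, no control event graded, and tiers sorted literally. Let u be the share graded Unlikely and l the share graded Likely.

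- Tier 1: E against E.
- Tier 2: triple = E × (1 − u); control = E. Ratio = 1 − u.
- Tier 3: triple = E × l; control = 0.

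E, u and l are assumptions; the protocol gives none of them. With E = 20:

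| u | l | Tier 1 | Tier 2 (triple v control) | Tier 2 ratio | Tier 3 (triple v control) |
|---|---|---|---|---|---|
| 0.3 | 0.5 | 20 v 20 | 20 × 0.7 = 14 v 20 | 0.70 | 20 × 0.5 = 10 v 0 |
| 0.5 | 0.3 | 20 v 20 | 20 × 0.5 = 10 v 20 | 0.50 | 20 × 0.3 = 6 v 0 |
| 0.6 | 0.2 | 20 v 20 | 20 × 0.4 = 8 v 20 | 0.40 | 20 × 0.2 = 4 v 0 |

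With E = 50 the ratios are unchanged: tier 2 reads 35, 25 and 20 against 50, and tier 3 reads 25, 15 and 10 against 0.

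**4. Does this reach the primary result?** The primary outcome (stated under section 10) is the incidence of AEs and SAEs against control. Neither that statement nor the analysis in 8.9 selects events by the causality grade, and neither does tier 1.

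**5. Who makes the initial attribution?** Section 8.5 gives it to the medical doctor, advised by the DSMB. Appendix 10 gives it to the DSMB members. These two differ.

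A neighbouring mismatch matters for the repair: item 4.1 of the form offers Not related, Probably and Unlikely. It has no Likely category, so as printed it cannot supply the third tier in either arm.

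**The case against.** The strongest reply is that no passage says control events will not be graded. The trigger in 8.5 and the charter applies to any SAE, the form's causality item names no arm, the control arm repeats the same process, and control participants do eventually take all three drugs. All of this stands. It means that a one-arm rule is something a reader might infer from the grading sentence, not something the protocol establishes.

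A reader might also infer that severe but non-serious events carry no grade, because the grading sentence says serious. The documents do not support that. Sections 8.4 and 8.5 treat a severe event as a possible SAE, Appendix 4 sends reported severe effects to the SAE questions, and Appendix 5 has the investigator answer yes if any severe effect was registered, after which the causality item follows.

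The review by the PI, supervisors and monitors might be read as a third rival decider. It is a later review of investigations for which the nurses supply information. The real conflict is between 8.5 and Appendix 10.

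Finally, the handling of ungraded events could be left to an analysis plan that is not shown, and no decision rule uses the second or third tier. That lowers the stakes. It does not remove the inconsistency, because the protocol itself fixes both the events to be graded and the tiers, and the two do not match.

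**Conclusion.** The point holds as an inconsistency in the protocol. The sentence that creates the grade names one arm; the tiers that consume it, and the other passages on attribution, do not. The opposite biases are conditional. They arise only if control events stay ungraded, ungraded events are kept in the second tier and left out of the third, and the arms are then compared on those tiers. Under those conditions, and with the assumed shares above, identical arms show a second-tier ratio of 0.70 to 0.40 and a third tier of 10 to 4 events against 0 (20 events in each arm). These figures illustrate the mechanism and do not forecast the trial.

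It would be too strong to say that the trial has no control comparator for severe and serious events, or that its main conclusion is biased: the first tier gives that comparison unfiltered, and the primary outcome does not depend on the grade. The matter is secondary but worth correcting before the data are collected, since a grade not made in the field is hard to recover even-handedly afterwards.

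**What to change.** 1. In section 8.5, change the subject of the grading sentence to *severe adverse events and serious adverse events in either arm*.
2. Grade both arms on the same form. In Appendix 5, reword item 3.5 so that it asks about the drugs taken in that round and fits each control round, and align the response options of item 4.1 with the scale in 8.5.
3. State that each of the three tiers is reported by arm.
4. Reconcile section 8.5 with Appendix 10 so that both name the same party for the initial attribution.

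The cost is wording in 8.5, Appendix 5 and Appendix 10, plus causality forms for a small number of control-arm events. Sample size, schedule and primary analysis are unchanged.
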